Following successful allocation to one of the three groups, the participants will be required to breathe in the upright sitting position before commencing the exercise using the most convenient respiration method. A volume-incentive spirometer (Coach 2 device), which enables the patient to inhale air through a mouthpiece and corrugated tubing attached to plastic bellows, will be used for the inspiratory exercise, with the volume of air displaced indicated on a scale located on the device enclosure (Kumar et al. 2016). The procedure will be demonstrated to the participant to ensure that it is well understood before commencement. After the participants have achieved the maximum volume, they will be instructed to hold the volume of air attained on the scale constant for 3–5 sec before exhalation (Zayed, Ahmed & Salem 2017). The participants will repeat the exercise three times to complete one set; three sets will be performed up to a maximum of 10 attempts. One minute of rest will be given between sets to reduce fatigue. The participants will leave after the following musculoskeletal assessment: The musculoskeletal assessment will involve screening of the participants’ musculoskeletal system for possible pain, swelling or limitation in joint range of motion. The procedure will be stopped whenever the subject feels dizziness or experience pain in the chest. The procedure will be repeated three times a week for 12 weeks. The MRC dyspnoea scale, 6MWT and PFSDQ-M will be conducted fortnightly during the study period.

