Following successful allocation, the participants will be required to breathe in the upright sitting position before commencing the exercise using the most convenient respiration method. In an upright sitting position, the participants will be asked to breathe in air through the nose to the maximum, then breathe out into a standard peak flow meter. The peak flow cursor will be adjusted to zero, and participants will be instructed to avoid touching the cursor during the exercise. The procedure will be demonstrated to the participants to ensure that it is well understood before commencement. They will be required to wrap their mouth tightly around the mouthpiece of the peak flow meter, to prevent the slippage of air around the corners of the device, then breathe out maximally into the peak flow meter as hard and as fast as possible (Adeniyi & Erhabor 2011). The effort will be noticed on the cursor. The cursor will be returned to zero, and the exercise will be repeated three times to complete one set. A total of three sets will be performed up to a maximum of 10 attempts. One minute of rest will be given between sets to reduce muscular fatigue. The procedure will be stopped if the participant feels dizziness or experiences pain in the chest. To avoid a Valsalva manoeuvre, participants will be asked not to hold their breath for more than 5 seconds following the maximum expiration. The participant will leave after the following musculoskeletal assessment. The musculoskeletal assessment will involve screening of the participants’ musculoskeletal system for possible pain, swelling or limitation in joint range of motion. The procedure will be repeated three times a week for 12 weeks. The participants MRC dyspnoea scale, 6MWT and PFSDQ-M will be conducted fortnightly during the study period.

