### Six-minute walk test

The 6MWT is a valid, responsive and reliable outcome measure frequently used in cardiac and pulmonary rehabilitation. It is often used to determine functional exercise capacity in patients undergoing cardiorespiratory rehabilitation. In a review of 167 articles between 1948 and April 2011 through Ovid MEDLINE, SPORTS, EMBASE, CINAHL, Cochrane reviews and Cochrane clinical trial, it revealed a responsiveness of the 6MWT in cardiac rehabilitation with an estimated mean difference of 60.43 m (95%, confidence interval 54.57 m – 66.30 m; *p* < 0.001) and moderate evidence of repeatability (Bellet, Adams & Morris 2012). A study by Brown and Nathan (2018) revealed a strong correlation between clinical outcomes and 6MWT distance in patients with chronic respiratory diseases.

The 6MWT will be performed according to the standardised procedure, and the first author (PI) who will be blinded to group allocation will supervise the process. The participants will be asked to walk at their maximum pace along a 30 m-long straight road. They will not be given any encouragement; the patient’s symptoms may limit the test. Therefore, if there are any signs of significant distress, such as dyspnoea, dizziness, angina or skeletal muscle pain, the participant will be asked to stop and sit down. The participants will only be allowed to continue upon alleviation of the discomfort. The total distance the participants cover will be recorded in meters (Du Bois et al. 2011). The procedure will be repeated at a 2-week interval for the duration of our study.

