### Data analysis

The Statistical Package for Social Sciences (SPSS Inc, Chicago, Illinois, United Sates) version 26.0 for windows package programme will be used to analyse data. Descriptive statistics of mean, standard deviation, frequencies and percentages will be used to summarise the results. Bar charts, pie charts and histograms will be utilised for pictorial illustration. A multivariate analysis of variance (MANOVA) will be used to compare the outcome pulmonary function variables (FEV_1_, FVC, FEV_1_/FVC, PEFR) and QoL (6MWT, MRC dyspnoea scale score and PFSDQ-M score) among groups, while the Bonforreni’s *t*-test will be utilised for post hoc analysis to detect where significant changes occurred in the outcome variables. Dependent t-tests will be used to compare the pre- and post-test results within variables while independent t-tests will be used to compare the outcome variable among the study and control groups. The level of significance will be set at *p* ≤ 0.05.

The study does not potentially involve risk or harm, as all interventions can only be performed within the limit of the patient’s tolerance. However, participants may experience mild discomfort because of the exercise, including temporary muscle soreness, increased heart rate, blood pressure, sweating and dizziness. All necessary care will be in place to prevent the occurrence of any adverse event. However, in case of a report of serious adverse events (e.g. comorbidities, injuries, persistent excruciating pain, dizzy spells, headache, etc.) after the intervention or at any point during the trial, we would consider unblinding the participant to the intervention for their safety. Additionally, the participants will be instructed to report adverse events to the first author PI or the physiotherapist supervising their group. To ensure adequate supervision, participants per group to be attended in a day will be limited to a maximum of three. Arrangements will be made with the Accident and Emergency units of the research site to provide a standby medical team. The University of KwaZulu-Natal insurance scheme on clinical trials has fully covered participants in this type of study.

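### Dizziness is listed both as an expected mild effect and as an example of a serious adverse event, and adverse-event reports may go to the blinded supervisor of the six-minute walk test

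*Protocol article*

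**What the plan says.** The safety text sits in the second paragraph of the section Data analysis. It first describes what the exercise may bring on: "participants may experience mild discomfort because of the exercise, including temporary muscle soreness, increased heart rate, blood pressure, sweating and dizziness". Shortly afterwards it turns to serious events: "in case of a report of serious adverse events (e.g. comorbidities, injuries, persistent excruciating pain, dizzy spells, headache, etc". For these, "we would consider unblinding the participant to the intervention for their safety". It then sets the reporting line: "the participants will be instructed to report adverse events to the first author PI or the physiotherapist supervising their group".

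Dizziness appears in three other places. Under Inspiratory incentive spirometry: "The procedure will be stopped whenever the subject feels dizziness or experience pain in the chest". Under Expiratory incentive spirometry: "The procedure will be stopped if the participant feels dizziness or experiences pain in the chest". Under Six-minute walk test, the participant stops and sits down "if there are any signs of significant distress, such as dyspnoea, dizziness, angina or skeletal muscle pain" and may go on once the discomfort has eased.

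On masking, the section Six-minute walk test says that "the first author (PI) who will be blinded to group allocation will supervise the process". The sections on the MRC dyspnoea scale and the PFSDQ-M again call the PI blinded, and name the PI as one of two people who answer participants' questions on those instruments.

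**The concern.** Two things in the safety text do not fit together.

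First, one symptom stands in both lists. A participant who becomes dizzy after a set of maximal breaths has had an expected mild effect by one sentence and an example of a serious event by another. Two physiotherapists could file the same episode differently, and each would be following the text. Because seriousness is what opens the question of unblinding, the filing has a consequence beyond the record. The device arms do repeated maximal manoeuvres that the controls do not, so the ambiguous events probably fall mostly there.

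Second, a person declared blinded is named as a recipient of adverse-event reports. Controls use no device. A participant who tells the PI about a complaint from the breathing exercise has in effect said that he or she is not a control. The PI then supervises that participant's walk test every two weeks. Walking distance depends on effort, so masking of the person who runs the test is worth protecting.

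**Working it through.** The point rests on comparing passages. The only arithmetic is a scale for how often the ambiguity could arise.

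**1. Is there a boundary between mild and serious dizziness?** In the mild list, the qualifier for short duration is attached to muscle soreness. In the serious list, the qualifiers for duration and intensity are attached to pain. Neither is clearly tied to dizziness or to dizzy spells, and headache has no qualifier. The serious list gives examples and ends openly, so it sets no limit. No duration, severity or outcome criterion in the article decides which list an episode belongs to.

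**2. Does the stopping text add a conflict?** No. Ending a session because of a mild, expected symptom is compatible with calling it mild. The conflict is between the two lists in Data analysis. The stopping text matters because it shows that dizziness is foreseen in both device arms.

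**3. Does dizziness point to an arm?** Only in part. Every arm does forced spirometry at its visits and every arm walks, and the walk-test section foresees dizziness there too. Dizziness alone therefore does not identify an arm. A complaint that the participant links to the device exercise does separate device arms from control, although it need not separate the two devices.

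**4. Can the report reach the blinded person?** Yes. The reporting sentence offers the PI or the group's physiotherapist. The walk-test section names the same PI as blinded supervisor.

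**5. Scale.** Inputs from the article:
- sessions per participant: three a week for 12 weeks, 3 × 12 = 36;
- device-arm participants: two device arms × three impairment classes × six per cell (Abstract, Method), 2 × 3 × 6 = 36;
- device sessions: 36 × 36 = 1,296.

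The article gives no dizziness rate, so the rate q per session is assumed. Expected episodes = 1,296 × q. Chance of at least one episode in a participant, if sessions are independent = 1 − (1 − q)^36.
- q = 0.1%: 1.3 episodes; 1 − 0.999^36 = 0.035, or about 1.3 of 36 participants.
- q = 1%: 13 episodes; 1 − 0.99^36 = 0.30, or about 11 of 36.
- q = 2%: 26 episodes; 1 − 0.98^36 = 0.52, or about 19 of 36.
- q = 5%: 65 episodes; 1 − 0.95^36 = 0.84, or about 30 of 36.

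These are episodes that would have to be classified. They are not serious events or unblindings. If dizziness clusters in a few people, fewer participants are affected for the same number of episodes.

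**6. Does any figure in the plan depend on this?** No. The sample-size output reproduces: with nine groups, six measurements and s = 5, the non-centrality is 0.35² × 51 × 5 = 31.2375, the denominator degrees of freedom are 5 × (51 − 9 − 5 + 5) = 210, and the power is 0.801, as stated. No safety quantity enters it.

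**The case against.** The strongest reply is that the serious list names kinds of event that may turn out serious, with the word serious governing all of them. On that reading a dizzy spell counts only when it is serious, and no episode has to be filed twice. That reading is possible, but the text does not compel it: unqualified headache in the same list, and the absence of any criterion, leave the choice open.

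A second reply is that a journal article may leave definitions of seriousness and severity grading to the full protocol, which is not shown. This is right, and the absence of definitions is not the complaint. The complaint is that the two lists, as printed, overlap.

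A third reply is that the masking harm is limited. Participant masking is weak in any case, because controls use no device. Reports may go to the physiotherapist and never reach the PI. The walk test follows a standard procedure without encouragement. All of this stands and limits the size, but it does not explain why a blinded supervisor should be a named recipient.

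A reader might also infer more than the article supports:
- That dizziness carries three incompatible roles. Stopping a session for a mild symptom contradicts nothing.
- That dizziness triggers unblinding. The text only says that unblinding would be considered.
- That no valid count of serious events can be produced, or that the safety results become uninterpretable. The article plans no such count and no safety comparison.
- That listing comorbidities makes every participant a serious case. The lung or thoracic disease that qualifies a participant is the index condition.
- That leaving chest pain off the serious list is an error. The list is open-ended.

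**Conclusion.** The point holds in a limited form. The safety text puts dizziness among expected mild effects and dizzy spells and headache among examples of serious events, with nothing to separate them. The class of an event, and with it the question of unblinding, is left to undefined discretion, probably more often in the device arms than in the control arm. Separately, the reporting line can give the blinded walk-test supervisor information that a participant is not a control.

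The size is uncertain: about 1 to 65 episodes in 1,296 device sessions for assumed rates of 0.1% to 5%. The episode counts rest on that assumed rate and on full attendance by six participants per cell; the participant counts also assume independent sessions. The overlap in the text does not depend on the rate.

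No sample-size figure or error rate changes. The primary outcome, pulmonary function, is measured by a separate technician described as blinded and is not touched. The exposed outcome is the six-minute walk test and, to a lesser degree, the two questionnaires on which the PI answers questions.

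**What to change.** - Reconcile the mild and serious lists in Data analysis so that an event has one place. Keep seriousness (whether an event counts as serious) separate from severity (how intense it is). Check the result against the stopping text in the two spirometry sections. Which clinical rule applies, and when unblinding is warranted, is for the sponsor and the investigators to decide; this review does not choose it.
- Route adverse-event reports to the physiotherapist supervising the group and to the study physician (Examiner 1, named under Randomisation and blinding), and take the PI out of the first reporting line while the PI supervises the walk test as a blinded person.

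The cost is a few lines of protocol wording and a changed reporting line among staff already named. The drawback is that the PI receives safety information indirectly, through the study physician.

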**Method:**

Fifty-four patients aged 40 years and above with obstructive, restrictive or mixed respiratory impairments attending the respiratory clinic at the Lagos State University Teaching Hospital, Ikeja (LASUTH), will be recruited and assigned to three groups of 18 participants based on the class of respiratory impairment. Participants in each category of respiratory impairment will be subdivided into three groups. A final group of six participants per class of impairment will participate in the experiment. Our study will be a double-blind, randomised control trial with two intervention groups and one parallel placebo control group. Pulmonary function will be assessed before and after every procedure while the six-minute walk test (6MWT), Medical Research Council dyspnoea scale and the Pulmonary Functional Status and Dyspnea Questionnaire-Modified will be assessed fortnightly during our study. Data will be analysed using descriptive and inferential statistics and a repeated MANOVA; *p* < 0.05.

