### Control group

Placebo effect refers to treatment that is essentially not therapeutically effective (Rossettini et al. 2020).

Following successful allocation, participants will be required to breathe in the upright sitting position using a respiration method that is most convenient for them. An assessment of the participants’ musculoskeletal system will be conducted as a placebo immediately after their pulmonary function test is conducted. The musculoskeletal assessment will involve a medical screening of the participants’ musculoskeletal system for possible pain, swelling or limitation in joint range of motion. The participant will leave after the musculoskeletal examination. The procedure will be repeated three times a week for 12 weeks. The MRC dyspnoea scale, 6MWT and PFSDQ-M will be conducted fortnightly during our study period.

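### Adverse event reports may go to the blinded investigator who supervises the walk test, so a report can reveal the arm to an outcome assessor

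*Protocol article*

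**What the plan says.** The safety paragraph under Data analysis gives participants two people to report to: "participants will be instructed to report adverse events to the first author PI or the physiotherapist supervising their group". For serious events it adds that "we would consider unblinding the participant to the intervention for their safety", without saying who decides.

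The principal investigator (PI) also has a part in outcome assessment. Under Six-minute walk test, "the first author (PI) who will be blinded to group allocation will supervise the process". The sections on the MRC dyspnoea scale and the PFSDQ-M let respondents ask the PI or the second research assistant to clarify the instruments, and describe both as blinded.

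Spirometry is kept separate. The Spirometry section assigns it to a certified technician who is blinded to allocation and is not named as a recipient of adverse event reports. The Sample size calculation section names pulmonary function as the primary outcome.

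The procedures differ openly between arms. The inspiratory arm inhales through a volume device and holds; the expiratory arm blows hard into a peak flow meter; the control arm uses no device. For controls, "An assessment of the participants’ musculoskeletal system will be conducted as a placebo immediately after their pulmonary function test is conducted".

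**The concern.** A blinded assessor should not be on a channel that carries information about allocation. Adverse event reports are such a channel here, because an ordinary account of when and how a symptom began will often mention the device or the manoeuvre.

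The walk test is the outcome most open to influence. It depends on effort, and the participant is asked to stop when distress appears and may resume once it eases, in a process that the PI supervises. Dizziness is both one of those signs of distress and one of the expected effects of the exercise listed in the safety paragraph. A PI who has heard that a participant became dizzy while blowing into the meter could, without intending to, handle that participant's walk differently. The walk distance, MRC score and PFSDQ-M score appear in both specific objectives and in the planned MANOVA, so the loss would not be trivial.

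**Working it through.** The plan gives no figure for adverse events or for assessor bias, so there is none to reproduce. The check sets the sections side by side and then counts exposure.

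**1. Do the roles overlap?**

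| Role | Person named | Section |
|---|---|---|
| Receives adverse event reports | PI or supervising physiotherapist | Data analysis |
| Supervises the walk test, declared blinded | PI | Six-minute walk test |
| Clarifies the questionnaires, declared blinded | PI or second research assistant | MRC dyspnoea scale; PFSDQ-M |
| Measures spirometry, declared blinded | Certified technician | Spirometry |

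The PI is in the first three rows. The technician is only in the last.

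**2. Can a report reveal the arm?** Yes, if it describes the exercise. Inhaling and holding points to the inspiratory arm, forceful blowing to the expiratory arm, and the absence of any device to control. A bare report of headache or soreness would not reveal it. Whether a given report does so depends on its content, which nothing in the article restricts.

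**3. Is the conflict stated, or only inferred from silence?** It is stated. The article gives both the reporting route and the blinding. A fuller protocol could resolve the conflict, but the published text contains both statements as they stand.

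**4. How large is the exposure?**

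- Participants with the route open to them: all 54.
- Walk tests: 12 weeks ÷ 2 = 6 fortnightly tests, or 7 if one is also done at baseline (an assumption). 6 × 54 = 324; 7 × 54 = 378.
- Sessions: 3 × 12 = 36 per participant, and 36 × 54 = 1,944 in all. With 6 per class in three classes, each therapy arm has 18 participants, so 18 × 36 = 648 sessions are control sessions and 1,944 − 648 = 1,296 involve a device.

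These are counts of opportunity. The number of reports that would reach the PI, the share that would reveal an arm, and the effect on walking distance are all unknown.

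**The case against.** The strongest reply is that only a possibility has been shown. Participants may report to the physiotherapist instead, who is at hand during sessions. A report need not mention the device. The PI gives no encouragement during the walk, which closes a main route by which an unblinded supervisor could affect it, and the result is a distance in metres. The second research assistant introduces the questionnaires and participants answer for themselves; the PI only clarifies on request. Participants know what they do in their sessions and meet the PI every fortnight, so rerouting reports cannot by itself secure the blind.

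All of this stands, and it limits the likely size. It does not remove the conflict: the article tells participants that they may bring such reports to a blinded assessor, and withholding encouragement does not remove the judgement about when a walk should pause.

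A reader might go further and infer that harms will be under-counted, because the end-of-session assessment is a "screening of the participants’ musculoskeletal system for possible pain, swelling or limitation in joint range of motion", while the safety paragraph expects discomfort "including temporary muscle soreness, increased heart rate, blood pressure, sweating and dizziness". The documents do not support that conclusion. The musculoskeletal assessment is not the only scheduled check, since "Pulmonary function will be assessed before and after every procedure". The screen asks about pain, so it can pick up soreness, and dizziness and chest pain are stop triggers in both device procedures, in supervised sessions. This is also a condensed article: a solicited checklist or event form may be in the full protocol, which is not shown. Nor does it follow that harms cannot be compared between arms. The control arm has no exercise to stop, the same musculoskeletal assessment is done in all three arms, and no stated objective is a comparison of harms.

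**Conclusion.** The point holds as a risk to assessor blinding. The PI is a named recipient of adverse event reports and also a blinded assessor, and the arms differ enough for an ordinary report to reveal allocation. The outcomes at risk are the six-minute walk and, to a lesser degree, the MRC scale and the PFSDQ-M. The primary spirometry outcome is not affected.

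It would be too strong to say that the blind is broken; the text shows only that it can be. The counts of 324 to 378 walks and 1,296 device sessions bound the exposure and say nothing about the amount of bias. The conclusion assumes that some participants will use the PI route and that some will describe the exercise when they do. It is worth correcting because the change is small and an assessor's knowledge of the arm cannot be undone later.

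**What to change.** Change the reporting sentence in the safety paragraph so that participants report adverse events to the physiotherapist supervising their group and to a physician who assesses no outcome. The study physician who screens for eligibility (Examiner 1) is a candidate. The article describes that role only at screening, so availability during the trial needs confirming. State that the PI receives only information that does not reveal the arm, unless formal unblinding is needed for safety, and say who makes that decision.

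The cost is one revised sentence and a short briefing of participants and staff. The downside is that the PI has less direct contact with event reports during the trial.

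As an optional addition, the existing end-of-session assessment could ask about the effects named in the safety paragraph, in the same words in all three arms. This is only a suggestion, since the full protocol may already contain it. It would lead to more minor events being recorded.
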